### Outline of the interventional bundle

The interventional bundle will consist of both pre-hospital and in-hospital components. Each of these will have core components that will be consistent across the seven study centres and adaptable components for optimisation to the local context (
Table 1). The content and detail of the core and adaptable components will be further defined utilising the results of the systematic review, qualitative study and Delphi process. A summary of the drivers to achieving a reduction in gastroschisis mortality is summarised in
Supplementary File 1
^110^.

**Table 1. T1:** An outline of the core and adaptable components of the interventional bundle.

Pre-Hospital	In-Hospital
Core	
A pre-hospital management protocol will be implemented at first and second level healthcare facilities (both government and private) that refer patients with gastroschisis to the study centres. These will be identified by the study leads at each site. The protocol will include: • Covering the bowel in clear plastic • Administering intravenous (IV) fluids • Keeping the neonate warm • Transferring to the study centre as soon as possible	• Use of a standardised protocol for care. • Neonatal resuscitation and ward care including IV access, IV fluids, maintenance of normothermia, appropriate antibiotics, regular monitoring and infection control. • Gastroschisis reduction and sutureless closure using a preformed silo, or equivalent, and avoidance of neonatal anaesthesia and surgery. • Early establishment of breastfeeding and enhanced enteral feeding programme.
Adaptable	
The method of dissemination and implementation of the pre-hospital management protocol will vary at each centre according to the optimal strategy as determined by the local team. Strategies include: • Wide dissemination of a guideline, leaflet and poster detailing the protocol with pictorial representations of the steps involved via post +/- back-up with telephone communications. • In addition to the above, site visits to selected referral centres for education and training to enhance implementation of the protocol. Visits and training will be undertaken by local MDT members and the principal investigator. • As an alternative to visiting referral hospitals, a gastroschisis study day at the study centre with MDT members from referral hospitals invited for education and training to enhance implementation of the protocol. • Dissemination of the protocol through existing government health policy pathways. • Radio and/or television campaign.	• Administration of a short period of parenteral nutrition for neonates who have survived to 7-days of life. • Maternal involvement in monitoring and basic management. • Management of neonates with gastroschisis on the neonatal ICU if available.

### Implementation of the interventional bundle

***Study design.*** A hybrid type 2 effectiveness-implementation pre-post study design will be utilised, which focusses equally on the effectiveness of the intervention through analysing clinical outcomes and effectiveness of the implementation through analysis of the service delivery and implementation outcomes
^111^.

The theoretical underpinning of the intervention and implementation strategy is based on the normalisation process theory (NPT)
^112^. This is a theory developed by implementation researchers in order to provide explanation and understanding of how a novel intervention becomes standard practice within a healthcare setting
^113–
115^.
Table 2 highlights the four constructs of the NPT and how they are addressed in the study design. The associated validated survey, NoMAD, will be utilised to evaluate MDT members opinions on each of these four areas at the end of the MDT training day (detailed below) and deficient areas will be actively targeted for improvement during the 4-week in-country implementation phase (
Supplementary File 2)
^110,
116^. The survey will be repeated at the end of the study to assess if and how perceptions have changed between implementation and study completion.

**Table 2. T2:** Normalisation process theory constructs used in the study design.

Normalisation Process Theory Constructs	How these will be addressed in the study
**Coherence:** • Participants distinguish the intervention from current ways of working • Participants collectively agree about the purpose of the intervention • Participants individually understand what the intervention requires of them • Participants construct potential value of the intervention for their work	• Involvement of all key MDT members in the development of the study and interventional bundle to be implemented • MDT simulation training (detailed below) • Through raising awareness about the possibility of improved outcomes using examples from other LMIC settings (through sharing the results of the systematic review and qualitative study with MDT members and discussion during the Delphi process consensus meeting, in-country co-development meeting and MDT training day). A leaflet will be developed and distributed amongst MDT members detailing successful gastroschisis management initiatives in other LMIC settings.
**Cognitive participation:** • Key individuals drive the intervention forward • Participants agree that the intervention should be part of their work • Participants buy-in to the intervention • Participants continue to support the intervention	• Study leads have requested participation in the study from each site • Some additional team members have already been identified with an interest to participate in the study • Identification of key individuals from the MDT to participate in the qualitative study and Delphi process • In-country co-development meeting to ensure local acceptability and feasibility and to provide local ownership
**Collective action:** • Participants perform the tasks required by the intervention • Participants maintain their trust in each other’s work and expertise through the intervention • The work of the intervention is appropriately allocated to participants • The intervention is adequately supported by its host organisation	• Locally determined roles and responsibilities within the study • Fidelity will be monitored and problems adhering to the protocol discussed and troubleshooted at the monthly MDT meetings • MDT simulation training to practice and trouble shoot in the simulated setting prior to implementation in practice • Inclusion of the hospital management in the development process, in-country co- development meeting and monthly MDT meetings
**Reflexive Monitoring:** • Participants access information about the effects of the intervention • Participants collectively assess the intervention as worthwhile • Participants individually assess the intervention as worthwhile • Participants modify their work in response to their appraisal of the intervention	• Real-time study outcomes and fidelity will be fed back to the MDT on a monthly basis and any problems with implementing components of the protocol will be discussed and troubleshooted • Challenges and successes from other study teams will also be shared so that teams can learn from each other’s experience

The Expert Recommendations for Implementing Change (ERIC) compilation of implementation strategies was utilised in the study design; 48 of the 73 strategies have been incorporated
^117^. The majority of chosen strategies rank as both important and feasible in the concept mapping study by Waltz
*et al*.
^118^. The following guidelines have been complied with to optimise the study design, evaluation and planned reporting: Standard Protocol Items: Recommendations for Interventional Trial (SPIRIT); Medical Research Council guidance on developing and evaluating complex interventions; Standards for reporting implementation studies (StaRI); Template for Intervention Description and Replication (TIDieR); and Standards for Quality Improvement Reporting Excellence (SQUIRE)
^119–
125^.

***Study sites.***

The study sites include seven tertiary paediatric surgery centres as follows:
1) Korle-Bu Teaching Hospital, Accra, Ghana2) Tamale Teaching Hospital, Tamale, Ghana3) Komfo Anokye Teaching Hospital, Kumasi, Ghana4) University Teaching Hospital, Lusaka, Zambia5) Arthur Davison Children’s Hospital, Ndola, Zambia6) Kamuzu Central Hospital, Lilongwe, Malawi7) Muhimbili National Hospital, Dar es Salaam, Tanzania

The study sites were included based on the following criteria:
Presence of a local champion/ study lead who requested/ agreed to participate in the studyTertiary Paediatric Surgery Centre where patients with gastroschisis are managedAt least 1–4 cases of gastroschisis per monthAbove 90–95% mortality from gastroschisis at baseline

***Stakeholders.*** Stakeholders at micro (patient/ parents), meso (healthcare facility teams) and macro (regional/ national) levels will be incorporated, with the main interventions being at the micro-meso level. The key stakeholders are summarised in
Table 3. All members of the MDT caring for neonates with gastroschisis are included as stakeholders. The study leads from each centre have identified a lead nurse and neonatologist and/or paediatrician and have held local team meetings to discuss and contribute to the study design and protocol. The study leads, lead nurse and lead neonatologist and/or paediatrician will be invited to participate in the qualitative study and Delphi process. The principal investigator (PI) will meet in-person with the study lead, lead nurse, lead neonatologist and/ or paediatrician, hospital management and the wider MDT involved in caring for neonates with gastroschisis for a co-development meeting when in-country. This will finalise the adaptable components for the interventional bundle. All in-hospital stakeholders will be involved in the implementation of the interventional bundle and follow-up MDT meetings to monitor progress and troubleshoot.

**Table 3. T3:** Key stakeholders for the pre-hospital and in-hospital components.

Stakeholders for pre-hospital component	Stakeholders for in-hospital component
Regional and national health boards Hospital management Nurses, doctors, surgeons and allied health professionals in district hospitals Parents of neonates born with gastroschisis	Paediatric and general surgeons Surgical residents, house officers/interns, medical students, medical officers Neonatologists, paediatricians, trainees Nursing supervisor, nurses Gastroenterologists, anaesthetists, dieticians Hospital management Parents of neonates born with gastroschisis

### Patient population

***Inclusion criteria.*** all neonates presenting primarily to the study centre with simple gastroschisis regardless of weight, gestational age or co-morbidities. Neonates with simple gastroschisis do not require surgical intervention and have the potential to be successfully managed with cotside reduction using a preformed silo and sutureless closure without the need for an anaesthetic.

***Exclusion criteria.*** all neonates with ‘complex gastroschisis’ requiring surgical intervention for bowel necrosis, perforation, atresia or other reason.

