### Sample size

It is estimated that between 240 to 384 patients with gastroschisis will present to the seven study centres during the 2-year data collection period (
Table 4). An estimated 75% of the neonates with gastroschisis should fulfil the inclusion criteria within the context of the study sites, equating to between 180 and 288 patients in the study in total (67–109 pre-intervention and 113–179 post-intervention). A successful pre-hospital component of the study may result in more patients presenting with simple gastroschisis and hence more being eligible for study inclusion.

**Table 4. T4:** The estimated number of gastroschisis cases per month at each of the study centres.

Site	Estimated no. cases/month	Dates for pre- intervention data collection at each site (total no. months)	Minimum no. pre-intervention cases,	Maximum no. pre- intervention cases	Timeframe for intervention implementation at each site in 2019	Dates for post- intervention data collection at each site (total no. months) *	Minimum no. of post- intervention cases	Maximum no. of post- intervention cases
**Korle-Bu TH,** **Ghana**	1	Oct 2018–May 2019 (7 months)	7	7	May 13 ^th^ – June 7th	May 2019 – Oct 2020 (17 months)	17	17
**Tamale TH, Ghana**	1–2	Oct 2018–June 2019 (8 months)	8	16	June 10 ^th^ – July 5th	June 2019 – Oct 2020 (16 months)	16	32
**Komfo Anokye TH,** **Ghana**	1	Nov 2018–July 2019 (8 months)	8	8	July 8 ^th^ – Aug 2nd	July 2019 – Nov 2020 (16 months)	16	16
**University TH** **Lusaka Zambia**	2–4	Nov 2018–August 2019 (9 months)	18	36	August 12 ^th^ – Sept 6th	Aug 2019 – Nov 2020 (15 months)	30	60
**ADCH, Zambia**	1	Jan 2019–Sept 2019 (8 months)	8	8	September 16 ^th^ – Oct 11th	Sept 2019 – Jan 2021 (16 months)	16	16
**KCH, Malawi**	2–4	Dec 2018–Oct 2019 (10 months)	20	40	October 21 ^th^ – Nov 15th	Oct 2019 – Dec 2020 (14 months)	28	56
**MNH, Tanzania**	2–3	Jan 2019–Nov 2019 (10 months)	20	30	Nov 25 ^th^ – Dec 20 ^th^	Nov 2019 – Jan 2021 (14 months)	28	42
**TOTAL**	**10 – 16**	**60 months**	**89**	**145**	**8 months**	**108 months**	**151**	**239**
**No. of patients** **with simple** **gastroschisis**	**8–12**		**67**	**109**			**113**	**179**

*Each site will collect 24 months of data in total

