## Data collection

### Clinical outcomes

***Primary outcome.***

1) All-cause, in-hospital mortality.

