***Secondary outcomes.***

1)   Major complication within 30-days of primary intervention
^1^: secondary bowel ischaemia, necrosis or perforation requiring resection
^2^, abdominal compartment syndrome
^3^ or need for further unplanned surgical intervention.

2)   Length of hospital stay amongst survivors (days).

3)   Time to full enteral feeds (days).

4)   Need for ventilation (yes/ no).

5)   Duration of ventilation (within 30 days of primary intervention in days).

Patient data will be collected on patient demographics, antenatal care, pre-hospital care, clinical condition on arrival, resuscitation, intervention (for bowel reduction and closure), ward care and outcomes (
Supplementary File 5)
^110^.

***Study impact on neonates with other congenital anomalies.*** The all-cause in-hospital mortality pre- and post- intervention will be determined for neonates presenting for the first time with anorectal malformation and intestinal atresia to see if there are indirect benefits for other patients requiring a similar package of neonatal surgical care.

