^132^.

***Coverage.*** The proportion of eligible patients who actually receive the intervention will be determined through the data entered into REDCap on all patients presenting with gastroschisis. Neonates with simple gastroschisis included within the study will have all data points completed. Neonates with complex gastroschisis excluded from the study intervention will have baseline data collected on the following: patient demographics, pre-hospital care and outcomes.

***Cost.*** The average cost per patient with gastroschisis will be estimated at the study centres, pre- and post-intervention. The implementation costs will also be calculated. The number of disability-adjusted life years (DALYs) averted through implementation of the interventional bundle will be calculated. The previously utilised disability-weight of 0.2 will be used for surviving neonates with gastroschisis where 0 is no disability and 1 is death
^2^. The cost in US$ per DALY averted will be calculated.

***Sustainability.*** The current intervention and implementation strategy have been evaluated for potential sustainability using the NHS Quality Improvement Sustainability Model
^133^. It scored 69.5/100 (19.8/31.3 for process, 43.1/52.4 for staff and 6.6/16.5 for organisation). A score above 55 is deemed ‘reason for optimism’. This evaluation has highlighted the need to set up a monitoring process beyond the life of the study, involve organisation leaders throughout the study process, to align the project with the team and organisation’s other strategy aims for improvement and to ensure facilities and equipment utilised are sustainable long-term. A re-evaluation will be undertaken just prior to interventional implementation and again following completion of the study.

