### Study Steering Committee (SSC)

An SSC consisting of two academic paediatric surgery consultants will independently oversee the project to ensure it is ethically sound throughout (
Supplementary File 8)
^110^. They will have access to the anonymous patient data collected in real time. If any major complications or deaths occur that may be associated with the intervention, these will be discussed and addressed between the SSC and study teams.

It is unlikely that the interventional care bundle will worsen outcomes compared to the current situation of above 95% mortality across the study centres. The main potential risk is bowel ischaemia related to incorrect application of the silo from either torsion of the vessels, use of a silo that is too small or an abdominal wall defect that is too small requiring incision under local anaesthesia
^135^. Training will be provided to avoid this complication and to recognise the early signs of bowel compromise, with techniques to remedy the situation before irreversible ischaemia and necrosis occurs. Of note, studies have shown bowel ischaemia is just as common in neonates receiving primary closure; however, in the latter, the problem cannot be visualised and remedied as easily
^54,
55^. Overall, use of a preformed silo is less invasive than the alternative of surgical interventional and general anaesthesia and hence carries less risks to the patient, especially in a low-resource environment without the availability of neonatal intensive care facilities. Insurance will be provided through King’s College London for any harm caused to patients receiving the care in the study protocol.

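### The primary comparison covers only simple gastroschisis, a status the bundle may change and whose assessment time is not stated; fix that time and co-report mortality in all presenting neonates

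*Protocol article*

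**What the plan says.** The protocol article's Patient population section includes "all neonates presenting primarily to the study centre with simple gastroschisis regardless of weight, gestational age or co-morbidities". It excludes neonates with complex gastroschisis "requiring surgical intervention for bowel necrosis, perforation, atresia or other reason". It describes simple cases as those that need no surgery, and gives no time at which this is judged. The Introduction (The problem) defines complex gastroschisis by bowel pathology alone, without reference to surgery.

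The Sample size section takes 75% of cases as eligible in both periods, but adds: "A successful pre-hospital component of the study may result in more patients presenting with simple gastroschisis and hence more being eligible for study inclusion".

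The primary outcome is "All-cause, in-hospital mortality", compared before and after by chi-squared test (Data analysis, Pre-post study analysis). One secondary outcome is major complication within 30 days of the primary intervention, which includes "secondary bowel ischaemia, necrosis or perforation requiring resection" and further unplanned surgery. The Study Steering Committee section states: "The main potential risk is bowel ischaemia related to incorrect application of the silo".

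Under Implementation outcomes, Coverage: "Neonates with complex gastroschisis excluded from the study intervention will have baseline data collected on the following: patient demographics, pre-hospital care and outcomes". The article states no pre-post mortality comparison that includes these neonates. The Aim is to reduce mortality from gastroschisis, without restriction to simple cases.

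**The concern.** There are two linked problems.

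**Eligibility depends on the intervention.** The bundle has a pre-hospital arm, and the Introduction attributes postnatal ischaemia and necrosis to delay and poor care before arrival. If that arm works, some infants who would have arrived complex arrive simple and enter the post-period denominator. In an unrandomised before-after study, a stable case definition is one of the few protections available, and this one can move with the treatment. The benefit of turning a complex case into a simple one also has no place in a simple-only mortality comparison.

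**The boundary between exclusion and outcome is not drawn.** Necrosis or perforation needing surgery appears in the exclusion rule and in the major-complication outcome, and bowel ischaemia is the named main risk of the silo. With no stated time point and an open-ended final category, seven sites could treat bowel loss after silo placement, or an atresia found late, in different ways. The choice changes the denominator of the primary outcome and the count of complications.

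**Working it through.** **Inputs from the protocol (Sample size).** Simple cases: 67 pre and 113 post (minimum), 109 and 179 (maximum). All cases: 89 and 151, 145 and 239. Design mortality: 95% to 79% (minimum), 95% to 83% (maximum). Complex share: 25%, the complement of the 75% eligible.

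**Assumptions not in the protocol.** Complex mortality 100%; complex share falling to 15%; 5 to 20% of post-period simple cases reclassified as surgical failures, all of whom die.

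**1. The protocol's own figures.** Power = Φ(h·√(n1·n2/(n1+n2)) − 1.96), with h = 2(arcsin√p1 − arcsin√p2).
- 67 v 113, 95% v 79%: 90.1%.
- 109 v 179, 95% v 83%: 90.7%.

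Both match the stated 90%, so this point involves no arithmetic error.

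**2. All presenting neonates, no change in case mix.**
- Pre: 0.75 × 0.95 + 0.25 = 96.25%.
- Post: 0.75 × 0.79 + 0.25 = 84.25%.
- Difference: 12.0 points, against 16 in simple cases.
- Power by the same formula: 89.1% (89 v 151). In the 83% scenario the difference is 9.0 points and power 89.9% (145 v 239).

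**3. Complex share falls to 15%; converted infants take 79% mortality.**
- Post, all: 0.85 × 0.79 + 0.15 = 82.15%; difference 14.1 points.
- Simple-only difference: still 16 points. The extra 2.1 points do not show there.

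**4. Same fall; converted infants keep 95% mortality.**
- Post, simple: (0.75 × 0.79 + 0.10 × 0.95)/0.85 = 80.9%; difference 14.1 points, down from 16.
- Post, all: 0.75 × 0.79 + 0.10 × 0.95 + 0.15 = 83.75%; difference 12.5 points, up from 12.0.

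Here the simple-only result looks worse while mortality in all neonates has improved.

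**5. Exclusion of post-period failures.** Observed mortality = (m − f)/(1 − f), where m is true mortality and f the fraction dropped.

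| f | true 79%, seen as | difference from 95% | true 95%, seen as | spurious fall |
|---|---|---|---|---|
| 5% | 77.9% | 17.1 points | 94.7% | 0.3 points |
| 10% | 76.7% | 18.3 points | 94.4% | 0.6 points |
| 20% | 73.8% | 21.3 points | 93.8% | 1.3 points |

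This mechanism can inflate a real effect. It cannot create a 12 to 16 point effect where there is none.

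**6. Unequal detection of complex cases.** Suppose 40% are recognised pre and 90% post (assumed), with simple mortality 95% in both periods.
- Pre: (0.75 × 0.95 + 0.15)/0.90 = 95.8%.
- Post: (0.75 × 0.95 + 0.025)/0.775 = 95.2%.
- Spurious fall: about 0.7 points.

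**The case against.** A reader might infer that the plan removes silo failures from the analysis. The documents do not support that. Inclusion speaks of neonates *presenting* with simple gastroschisis. Coverage describes complex cases as excluded from the intervention, which cannot apply to an infant already under a silo. The complication outcome is called *secondary* and is timed from the primary intervention, so it presupposes that such infants stay in. The footnotes to that outcome and the data collection form (Supplementary File 5) are not shown and may settle the timing. All of this stands: dropping failures is possible under the wording, not prescribed by it.

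A reader might also infer that pre-hospital benefit goes uncounted. That is too broad. Better condition on arrival among simple cases enters the primary mortality comparison, and pre-hospital process is measured and related to mortality under the service delivery outcomes. Only the prevention of complex disease is missed.

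Nor does the bias have one direction. Converted infants may be sicker than other simple cases, which works against the bundle (step 4). The Study Steering Committee section says ischaemia is as common with primary closure, so failures need not fall only in the post period. Unequal detection between periods is conjecture.

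Finally, the restriction has a stated reason: simple cases can be managed at the cotside without anaesthetic. That is a fair ground for keeping them as the primary population. It does not settle the missing time point, or the dependence on case mix that the protocol itself acknowledges.

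**Conclusion.** The point holds as a weakness that should be corrected, not as proof that the primary comparison is invalid. The primary population is defined by a status that the protocol says the bundle may change, and the rule has no stated time point and an open-ended last category.

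The sizes are illustrative. If the complex share falls from 25% to 15%, with complex mortality 100%, about 2 points of all-presenting benefit (12.0 to 14.1) do not show in the simple-only difference, which stays at 16 or shrinks to about 14 depending on how the converted infants fare. With mortality at 95% in both periods, exclusion of failures yields about 0.3 to 1.3 points, and unequal detection about 0.7. Neither could by itself produce the 12 to 16 points the study is sized to detect. The shift in complex share, the complex mortality, the reclassified fraction and the detection rates are all assumptions.

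**What to change.** - State in Patient population that simple or complex status is fixed at arrival, before the primary intervention, by the same rule in both periods.
- State that bowel loss, perforation or atresia found later is an outcome and never a reason for exclusion.
- Remove the open-ended final category of the exclusion, or define it.
- Keep simple cases as the primary population. Pre-specify a co-reported pre-post comparison of all-cause in-hospital mortality in all neonates presenting with gastroschisis, and report the complex share by period.

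The cost is wording and a little more analysis, since outcomes of complex cases are already entered in REDCap. The all-presenting effect may be diluted because complex cases are excluded from the study intervention: 12.0 against 16 points with no case-mix shift. The larger numbers almost make up for this in power (89.1% and 89.9%, against 90.1% and 90.7%). Replacing the simple-only primary population altogether would be a trade-off, and this point does not require it.
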